### Data analysis

2.13

The primary outcome (MDBF calmness subscale change from T0 to T1) will be analyzed using an ANCOVA model. The model will include the study group (4 arms for primary analysis: Groups 1–4) as the independent variable and the baseline MDBF score as a covariate to control for any initial differences and improve statistical power. This aligns with the principle of analyzing covariance to account for baseline variance. The primary contrast of interest is whether either of the two combination groups (1: Hypnosis + Bergamot, 2: Hypnosis + Lavender) differ significantly from the control groups (3: Hypnosis-only, 4: Minimal intervention) in adjusted mean relaxation at T1. We anticipate a significant overall group effect; planned pairwise comparisons with appropriate correction for multiple comparisons, if needed, will examine specific differences, especially 1 vs. 3, 2 vs. 3, and combined 1&2 vs. combined 3&4. The primary hypothesis will be supported if Groups 1 and 2 show statistically greater increases in relaxation than Group 3 and Group 4 (*p* < .05, two-tailed).

For Phase 2 conditioning effects, a similar ANCOVA or mixed-model approach will be used at T2. The analysis will focus on the four groups that underwent Phase 2 aroma testing (Groups 1, 2 with match vs. Groups 5, 6 with mismatch). We will compare relaxation outcomes at T2 among these, using T1 values as covariates. A significant difference (e.g., match > mismatch) on the MDBF relaxation change from T1 to T2 or on the Phase 2 VAS responses would support H2.1. We may also use repeated measurements ANOVA or multilevel modeling incorporating all three time points (T0, T1, T2) to examine group × time interactions across the full study duration. The VAS data from each session will be analyzed using linear mixed-effects models, which can handle multiple observations per participant. These models will test differences in immediate relaxation gain per session by group and can also model time trends (session number as a predictor) to see if there is a significant upward trend in pre-session relaxation over the 6 weeks for each group (learning effect).

All secondary continuous outcomes (anxiety, stress, sleep, well-being, worry scores) will similarly be analyzed via ANCOVA at T1 and T2 controlling for baseline, comparing the four main groups. We expect trends favoring the combined intervention, but these will be interpreted with caution and adjusted for multiple comparisons since multiple scales are involved. Moderator analyses (H2.3) will be exploratory by including interaction terms in the ANCOVA or regression models or conduct subgroup analyses splitting the sample by median age. Given the sample size (∼105 per arm planned), the trial is powered primarily for the main effect on the primary outcome; subgroup effects would have to be large to be detectable, so these findings will be descriptive.

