### Study groups

2.6

Participants are randomly assigned to one of six groups (arms) in a 1:1:1:1:1:1 ratio. Four groups are primary comparison arms for the main efficacy analysis at 6 weeks, and two additional groups are included for secondary analyses of conditioned stimulus specificity in Phase 2.

**Group 1: Hypnosis** + **Essential Oil (Bergamot).** Participants receive the self-hypnosis audio and inhale bergamot essential oil during each session in Phase 1. In Phase 2, they continue with bergamot oil only (no audio) on the same schedule. This is a conditioned stimulus (CS)-match condition where the same essential oil is used for conditioning and testing.

**Group 2: Hypnosis** + **Essential Oil (Lavender).** Participants receive the hypnosis audio plus lavender essential oil inhalation during Phase 1 sessions. In Phase 2, they use lavender oil only without hypnosis. This is the CS-match for lavender.

**Group 3: Hypnosis Only (No Oil).** Participants receive guided hypnosis sessions in Phase 1 with no aromatherapy. This controls for the effects of hypnosis alone. They do not use any aroma in Phase 2 either and effectively have no active intervention in weeks 7–8.

**Group 4: Minimal Intervention Control.** Participants do neither hypnosis nor essential oil in Phase 1. Instead, they may receive a minimal activity just to match time/expectation. This arm serves as a baseline and expectancy control. They also do not receive any aroma in Phase 2.

**Group 5: Hypnosis** + **Oil (Bergamot) → Switch to Lavender.** These participants start identical to Group 1 (hypnosis + bergamot oil in Phase 1). However, in Phase 2 they experience a CS-mismatch by switching to lavender without hypnosis. This group helps test if a different scent can trigger relaxation or if the effect is lost when the conditioned stimulus changes. It serves as a control for Group 1 in the conditioning analysis.

**Group 6: Hypnosis** + **Oil (Lavender) → Switch to Bergamot.** These participants mirror Group 2 initially (hypnosis + lavender in Phase 1), then switch to bergamot oil only in Phase 2, creating a CS-mismatch. This serves as a control for Group 2 to assess stimulus specificity.

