All groups 1, 2, 5, and 6 receive the full combined intervention (hypnosis + essential oil) in Phase 1, ensuring that Groups 5 and 6 have the same conditioning opportunity as their counterparts before the switch. Groups 3 and 4 allow us to isolate the effects of hypnosis itself (Group 3) and to account for any changes over time not attributable to the interventions (Group 4). Randomization is implemented via the SoSci Survey platform's built-in algorithm once participants are deemed eligible, ensuring allocation concealment. Because of the nature of the interventions, participants will know if they are using an oil or not (blinding is not feasible on the user level), but they will not be informed of the study hypotheses regarding which combination is expected to be most effective. The trial is single blinded in that the data analysts/statisticians will remain blind to group labels until after the primary analyses are completed, to prevent bias in outcome analysis.

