### Physiological subgroup

2.8

To complement self-reported outcomes with physiological data, the study includes an optional physiology component for a subset of participants. Up to 15 participants per group (approx. n≈90 total) who live in the Berlin/Brandenburg region will be invited to attend laboratory sessions at the Charité – Virchow Clinic Campus in Berlin. Electrophysiological measurements will be performed over a 15-min period during which the participant is at rest and in a supine position in the electrophysiological laboratory. During this period, the ECG and pulse are recorded using wearables. Electrophysiological measurements are to be recorded at two time points: initially at the baseline (T0) and subsequently following the six-week intervention period (T1). The ECG and pulse raw data indices were utilized to derive HRV and pulse wave variability (PWV), which are indices of autonomic nervous system (ANS) activity. The activity of the sympathetic nervous system (SNS), the parasympathetic nervous system (PNS), or both components of the ANS is indicated by these indices. In the course of each and every recording session, the participants were equipped with a Polar H10 chest-strap heart rate sensor (for the purpose of recording ECG for HRV) and a Polar Verity Sense optical pulse sensor (for the purpose of PWV via photoplethysmography). It is hypothesized that the response to the various 6-week interventions would be subject to change, and that the before-and-after effect would vary in the autonomous variables depending on the nature of the intervention. This methodology facilitates the representation of variation in dynamic changes across groups and over time. A comparison of the time points T0 and T1 will facilitate objective and quantitative mapping of the dynamic changes caused by the interventions. The autonomous measurements will facilitate the characterization of the interventions in terms of their mechanisms of action, and the extent to which each intervention leads to the assumed subjective improvement in relaxation/recovery (increased PNS). In addition, the study will elucidate the way this intervention enhances autonomic-vegetative function in the short term. The utilization of HRV and PWV in the time domain, in the frequency domain and nonlinear dynamics, has been demonstrated to be a reliable indicator of changes in sympathovagal balance (19). A greater HRV (particularly high-frequency HRV) and a slower PWV (which reflects vasodilation and reduced arterial stiffness) would suggest a shift towards parasympathetic dominance and relaxation. It is hypothesized that the combination of hypnosis and essential oils may result in increased relaxation, which is further enhanced by the intervention and over time from T0 to T1 in comparison to the hypnosis-only group. This is consistent with the hypothesis that deeper or more effective relaxation training is achieved through this method. The resultant phenomenon is evidenced by a decline in sympathetic tone and an augmentation in vagal tone, culminating in a state of profound relaxation and recuperation through the deactivation of the ANS.

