**Exploratory Hypothesis 2.3 (Moderators of Effect).** We will explore whether certain baseline factors moderate the intervention's effectiveness. Demographic factors like age, gender, or socioeconomic status might influence outcomes. For instance, it's possible that participants with higher initial anxiety, though still subthreshold, benefit more or less from the intervention, or that younger vs. older participants have different adherence rates. These analyses are exploratory and will be used to generate hypotheses for which subgroups respond best to this approach.

**Exploratory Hypothesis 2.4 (Physiological Effects).** We hypothesize that the combination of hypnosis and aromatherapy yields measurable physiological relaxation, reflected in increased parasympathetic activity or reduced sympathetic activity compared to hypnosis alone. In the laboratory subgroup, it is hypothesized that Group 1/2 (combined) will demonstrate larger increases in HRV, particularly high-frequency HRV, which is indicative of parasympathetic tone, and/or a greater reduction in heart rate and PWV from T0 to T1 than Group 3 (hypnosis only). This would suggest an additive effect of the essential oil on the body's relaxation response, consistent with objective evidence that an essential oil can modulate autonomic activity. However, given sample size limitations, this will be an exploratory outcome.

**Exploratory Hypothesis 2.5 (VAS Trajectory and Learning Effects).** By examining the VAS relaxation ratings collected before and after each session, we hypothesize that participants receiving the combined intervention will not only have larger acute relaxation gains per session on average than those in comparison groups, but they may also exhibit learning effects over time. A learning effect would manifest as gradually higher pre-session relaxation levels as weeks progress the participant's baseline state before each session improves, indicating they carry over some relaxed state or become more skilled at self-relaxation. We expect such effects might be most pronounced in those who undergo conditioning (Groups 1 and 2), potentially showing an upward drift in pre-session VAS scores and/or a plateau indicating habituation to relaxation. We will explore and graph these trajectories for insight into how the relaxation response develops with practice.

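### Groups 5 and 6 receive the same Phase 1 treatment as Groups 1 and 2, yet the primary, secondary-scale and H2.4 contrasts at T1 do not use them: a loss of efficiency, not a bias

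*Protocol article*

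**What the plan says.** **Treatment up to T1.** Study groups (2.6) states that "All groups 1, 2, 5, and 6 receive the full combined intervention (hypnosis + essential oil) in Phase 1". Of Group 5 it says "These participants start identical to Group 1 (hypnosis + bergamot oil in Phase 1", and it describes Group 6 as mirroring Group 2 at first. The four arms separate only in Phase 2, when Groups 5 and 6 switch oil. Allocation is equal across six arms. Timeline and assessments (2.7) has all participants complete the T1 survey.

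**Who enters the T1 analyses.** Data analysis (2.13) fixes the primary ANCOVA at "4 arms for primary analysis: Groups 1–4". Its named comparisons are 1 vs 3, 2 vs 3, and 1 and 2 combined vs 3 and 4 combined. The secondary scales "will similarly be analyzed via ANCOVA at T1 and T2 controlling for baseline, comparing the four main groups". H1 and H2.2 in Hypotheses (2.10) name only Groups 1 and 2 as the combined intervention. H2.4 predicts that "Group 1/2 (combined) will demonstrate larger increases in HRV" than Group 3.

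**Physiology.** Section 2.8 plans "Up to 15 participants per group (approx. n≈90 total" and records at T0 and T1 only.

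**Stated role of the extra arms.** Section 2.6 says "two additional groups are included for secondary analyses of conditioned stimulus specificity in Phase 2". It gives no reason for leaving their T1 data out of the efficacy contrasts.

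**Models that name no groups.** The Phase 1 session VAS models, the optional group by time model over T0, T1 and T2, and the moderator models do not say which arms they include.

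**The concern.** At T1 the six randomised arms represent only four treatments, two of them given to two arms each. For a question about Phase 1, the analysis that matches the design compares four treatments on all 630 participants. The plan compares four arms on 420. The estimate has the same target but is less precise than the trial's own data allow, most of all for the oil vs hypnosis-only contrasts, which isolate what the oil adds.

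Physiology shows this most clearly. Nothing is recorded after T1, so the lab data from Groups 5 and 6 cannot bear on conditioning in Phase 2. The only named contrast, H2.4, does not use them either. Up to 30 people would attend the laboratory twice without contributing to it.

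**Working it through.** **Inputs (Sample size calculation, 2.11, unless noted).** 105 per arm, N = 105 × 6 = 630; alpha 0.05 two-sided; f = 0.175, equated there to a pairwise d of about 0.35–0.40; covariate R² about 0.20; dropout up to about 35%. Up to 15 per arm in physiology (2.8).

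**1. The plan's own figure.** The stated calculation is a four-group ANCOVA with f = 0.175, R² = 0.20 and 80% power. By noncentral F, with λ = f²N/(1 − R²), df1 = 3 and df2 = N − 5, it needs 73 per group (90 with R² = 0), not 105. A two-group comparison at d = 0.35 and R² = 0.20 needs 104 per group, so 105 fits that reading. This is a separate matter. It means that d = 0.35 with R² = 0.20 is a fair basis for the pairwise contrasts below.

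**2. Share not used.** 2 × 105 = 210, and 210/630 = 33.3%.

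**3. Completers at the allowed dropout.** The article aims for 105 completers per arm but enrols 105 per arm. At 35% dropout, 105 × 0.65 = 68.25, so about 68 per arm.

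**4. Variance ratios, with n per arm (pooled / planned).**
- One oil vs Group 3: (1/2n + 1/n)/(1/n + 1/n) = 1.5/2 = 0.75. Variance falls 25%, standard error 13.4%.
- Both oils vs Group 3: (1/4n + 1/n)/(1/2n + 1/n) = 1.25/1.5 = 0.83. Variance falls 17%, standard error 8.7%.
- Both oils vs Groups 3+4: (1/4n + 1/2n)/(1/2n + 1/2n) = 0.75/1 = 0.75. Variance falls 25%, standard error 13.4%.

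The gain is limited because Groups 3 and 4 stay the same size.

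**5. Power.** Noncentral t with noncentrality d / [√(1 − R²) × √(1/n₁ + 1/n₂)], d = 0.35, R² = 0.20, alpha 0.05 unadjusted. Example for one oil vs Group 3 at 105 per arm: √0.80 = 0.894 and √(2/105) = 0.138, so the noncentrality is 2.83. With 210 vs 105 it is 3.27.

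| Contrast | 105 per arm: planned → pooled | 68 per arm: planned → pooled |
|---|---|---|
| One oil vs Group 3 | 81% → 90% | 62% → 75% |
| Both oils vs Group 3 | 90% → 95% | 75% → 82% |
| Both oils vs Groups 3+4 | 98% → 99.6% | 90% → 96% |

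The four-group omnibus test at f = 0.175 has 93% power at 105 per arm as planned. At 68 per arm it goes from 77% to about 87–96%, depending on the assumed pattern of means.

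**6. Sensitivity to multiplicity.** The article leaves correction open. If Bonferroni over the three named comparisons were used (alpha 0.05/3, an assumption for illustration), one oil vs Group 3 would go from 67% to 81% at 105 per arm and from 45% to 59% at 68.

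**7. Physiology.** Pooled oil vs Group 3 changes from 30 vs 15 to 60 vs 15: (1/60 + 1/15)/(1/30 + 1/15) = 0.083/0.100 = 0.83. Variance falls 17%. Without a covariate, the effect detectable with 80% power moves from d of about 0.91 to about 0.82.

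**The case against.** The restriction is deliberate and consistent. The abstract, design, hypotheses and analysis all describe a four-arm primary comparison, and Groups 5 and 6 were added for the Phase 2 specificity test. That stands as an account of why the arms exist. It does not explain why their T1 data should go unused.

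Three stronger readings are tempting, and the article does not support them.

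- **That the primary analysis is biased or invalid.** Groups 1–4 form a proper, prespecified randomised comparison.
- **That Groups 5 and 6 are left out of every T1 or Phase 1 analysis, or thrown away.** The VAS, group by time and moderator models name no groups, and the general physiology text in 2.8 speaks of the combination without limiting it to Groups 1 and 2. The T1 values of Groups 5 and 6 also serve as covariates in the Phase 2 analysis.
- **That the primary question is underpowered without pooling.** At 105 completers per arm the omnibus test and the combined contrast are already well powered on the article's assumptions. The larger gains come at 68 completers, which results from the missing dropout inflation and is a separate issue.

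There is also a real caveat. Randomisation makes the pairs of arms comparable at baseline, but pooling also needs them to be treated alike, and to behave alike, until T1. The article does not say when the second oil is sent or when participants learn of the switch. They know whether they use an oil, and the outcome is self-reported. A Groups 1–4 sensitivity analysis does not test this assumption directly. Comparing Group 1 with 5 and Group 2 with 6 at T1 does.

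**Conclusion.** The point holds as a loss of efficiency in the primary ANCOVA, the secondary-scale ANCOVAs at T1 and the H2.4 contrast. A third of the randomised participants received the treatment under test and supply the T1 outcome, but do not contribute to these contrasts.

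Pooling matters most for each oil against hypnosis alone, and more so if dropout approaches the level the article allows for. It matters little for the combined contrast at full completion. In physiology the gain is modest, and that analysis remains exploratory because Group 3 stays at 15.

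The power figures rest on the article's d = 0.35 and R² = 0.20, on unadjusted alpha, on equal dropout across arms, and on Groups 5 and 6 not knowing of the switch before T1. The change is worth making but is not a condition for a valid trial.

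**What to change.** For T1 and Phase 1 analyses (MDBF, the secondary scales, session VAS, HRV and PWV), define Phase 1 treatment as a four-level factor:

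- hypnosis + bergamot: Groups 1 and 5
- hypnosis + lavender: Groups 2 and 6
- hypnosis only: Group 3
- minimal intervention: Group 4

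Reword H1, H2.2 and H2.4 to match, and state which groups enter the VAS, group by time and moderator models. Keep the Groups 1–4 analysis as a sensitivity analysis. Report Group 1 vs 5 and Group 2 vs 6 at T1, with confidence intervals, as the direct check of comparability. State when participants in Groups 5 and 6 learn of the switch. Do not pool at T2, where the arms have received different oils, and leave the match vs mismatch analysis as planned.

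The cost is a change of wording in the protocol, analysis plan and registry entry, with no new participants or assessments. It should be fixed before unblinding, because adding arms afterwards would look data-driven. The article plans no interim analysis and keeps the analysts blind to group labels until the primary analyses are complete, so a documented change made before then remains credible. The remaining downside is small: if Groups 5 and 6 did learn of the switch early, the pooled estimate could be affected, and the checks above are there to show it.

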### Hypotheses

2.10

**Primary Hypothesis (H1—Efficacy).** After six weeks of intervention (T1), participants receiving self-hypnosis combined with essential oil inhalation (Groups 1 and 2) will demonstrate greater improvement in subjective relaxation, as measured by the Multidimensional Mood Questionnaire (MDBF), compared to participants receiving self-hypnosis without essential oil (Group 3) or a minimal-intervention control (Group 4).

**Primary Null Hypothesis (H0).** There are no differences between intervention groups in change in subjective relaxation from baseline to T1. **Primary Alternative Hypothesis (H1).** At least one intervention group differs from the others with respect to change in subjective relaxation from baseline to T1.

**Secondary Hypothesis 2.1 (Conditioned Relaxation).** In Phase 2, the essential oil alone will elicit relaxation in those groups that have consistent pairing in Phase 1. Specifically, participants in the CS-match conditions (Group 1 with bergamot, Group 2 with lavender) will show a significant increase in relaxation as measured by pre-post VAS and possibly MDBF from T1 to T2, when exposed to the essential oil alone, whereas those in CS-mismatch conditions (Group 5 and 6, who receive a different oil than used in training) will have smaller or no relaxation response. We hypothesize a stimulus-specific conditioning effect, meaning the relaxation response is tied to the particular essential oil used during training, not just any pleasant essential oil.

**Secondary Hypothesis 2.2 (Broader Psychometric Benefits).** The combined hypnosis + essential oil intervention will lead to greater improvements in other psychological outcomes compared to hypnosis alone or minimal intervention. We expect to see reductions in self-reported anxiety symptoms (lower GAD-7 scores), perceived stress (lower PSS-14), and worry (lower PSWQ-d) as well as improvements in sleep quality (lower PSQI) and overall well-being (higher WHO-5) in Groups 1 and 2 vs. Groups 3 and 4 at T1. This hypothesis posits that beyond immediate relaxation, the 6-week intervention confers broader mental health benefits (less anxiety and stress, better sleep and mood), echoing findings that combined mind-body interventions can positively affect multiple domains of functioning.

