### Sample size calculation

2.11

The sample size was determined based on the primary outcome. The team conservatively anticipated a medium effect size for the group difference (Cohen's *f* ≈ 0.175, which corresponds roughly to d ∼0.35–0.40 in pairwise terms) given prior results based on the prior study on healthy individuals (11). Power analysis (*α* = 0.05 two-tailed, 1 − *β* = 0.80) for a one-way analysis of covariance (ANCOVA) with 4 groups and baseline as covariate, assuming the covariate explains ∼20% of variance, indicated needing about N ≈ 105 participants per group to detect *f* = 0.175. Allowing for up to ∼35% dropout, due to the fully online nature and 8-week duration, we decided to increase the target enrollment to ensure at least 105 completers per arm. Including the two extra groups for the conditioning test, the total planned sample size is *N* = 630 (105 × 6). This large sample will provide adequate power not only for primary comparison but also to explore secondary endpoints. Interim analyses are not planned; all data will be analyzed after study completion. The qualitative data from open-ended questions will be analyzed using deductive-inductive qualitative content analysis to identify patterns and themes in participants' experiences. We will integrate quantitative and qualitative findings in interpretation to understand the intervention's impact under consideration of multiple perspectives.

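### The primary hypothesis has several non-equivalent success rules, and one planned comparison (Groups 1&2 vs 3&4) can be positive when the oil adds nothing

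*Protocol article*

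**What the plan says.** All statements concern change in MDBF calmness from T0 to T1.

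- Section 2.9 (Outcomes) makes the two combination groups against both control conditions the key comparison.
- Section 2.10 (Hypotheses) first gives a directional hypothesis: Groups 1 and 2 improve more than Group 3 *or* Group 4. It then gives a formal alternative, also labelled H1: "At least one intervention group differs from the others with respect to change in subjective relaxation from baseline to T1".
- Section 2.13 (Data analysis) opens with: "The primary contrast of interest is whether either of the two combination groups" differs from the control groups.
- The same section plans pairwise comparisons, corrected for multiplicity if needed, and singles out "especially 1 vs. 3, 2 vs. 3, and combined 1&2 vs. combined 3&4".
- It closes with the only sentence that says when the hypothesis counts as supported: "The primary hypothesis will be supported if Groups 1 and 2 show statistically greater increases in relaxation than Group 3 and Group 4", at two-tailed p < .05. It does not say whether the groups are pooled or compared pair by pair.

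Section 2.6 (Study groups) defines Group 3 as hypnosis without oil and Group 4 as neither. Section 2.11 computes 80% power "for a one-way analysis of covariance (ANCOVA) with 4 groups and baseline as covariate, assuming the covariate explains ∼20% of variance". That is a calculation for the omnibus test.

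**The concern.** These are different decision rules, so the same data could meet one and fail another. The text does not say which one governs.

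The pooled 1&2 vs 3&4 comparison adds a second problem. Section 2.6 has Group 3 isolate hypnosis and Group 4 capture change unrelated to the interventions. Averaging the two gives a comparator that is half hypnosis and half no hypnosis. If hypnosis works and the oil does nothing, the contrast is still positive. A significant omnibus test beforehand gives no protection, because Group 4 alone would drive it.

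At stake is whether a positive primary result shows that the combination beats both of its named comparators, or only that hypnosis beats no hypnosis. The power statement is also affected, because it belongs to the omnibus test and not to the rule in the success sentence.

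**Working it through.** **Inputs.** From section 2.11: two-sided α = 0.05, power 80%, four groups, covariate R² about 0.20, f = 0.175, and pairwise effect "which corresponds roughly to d ∼0.35–0.40 in pairwise terms". The number analysed per arm is n = 105, the stated completer target. Assumptions: outcome SD is set to 1, so residual variance is 0.8; the hypnosis-vs-minimal effect is not given, so d = 0.35–0.40 is borrowed from the pairwise range.

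**The plan's own figure.** Omnibus noncentral F with λ = 4n·f²/(1 − R²) and df = 3 and 4n − 5. For f = 0.175 and R² = 0.20, 80% power needs 73 per group, not 105. At 105 per group the power is 93%. So 105 is not reproduced by the calculation described. That is a separate matter and does not affect this point.

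**The pooled contrast with no oil effect.** Let the true means in Groups 1–4 be (d, d, d, 0).

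- Contrast = (d + d)/2 − (d + 0)/2 = d/2.
- SE = √(0.8 × (1/210 + 1/210)) = √(0.8/105) = 0.0873, with df = 420 − 5 = 415.
- d = 0.35: 0.175/0.0873 = 2.00, significant in favour in 52% of trials.
- d = 0.40: 0.200/0.0873 = 2.29, significant in favour in 63%.

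Multiplicity correction does not remove this. With Bonferroni over the three named comparisons the figures are 35% and 46%. With 68 analysed per arm (105 × 0.65, if the 35% dropout came out of the 105) they are 36% and 45% uncorrected. If hypnosis has no effect, the contrast is not distorted.

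**The same truth under each reading** (oil 0, hypnosis d = 0.35, 105 per arm; 400,000 simulated trials):

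| Reading of the rule | Met in |
|---|---|
| Either combination arm beats any control | 92% |
| Omnibus: some group differs | 84% |
| Pooled 1&2 beats pooled 3&4 | 52% |
| Either combination arm beats both controls | 4.5% |
| Pooled 1&2 beats 3 and beats 4 | 2.5% |
| All four pairs (1 and 2 each beat 3 and 4) | 0.4% |

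**Power when the oil adds d over Group 3** (105 per arm, R² = 0.20):

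| True effects | All four pairs | Pooled 1&2 beats 3 and beats 4 |
|---|---|---|
| Oil 0.35, hypnosis 0 | 54% | 83% |
| Oil 0.40, hypnosis 0 | 72% | 93% |
| Oil 0.35, hypnosis 0.35 | 70% | 90% |
| Oil 0.40, hypnosis 0.40 | 83% | 96% |

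In the first row the means are (0.35, 0.35, 0, 0), so f = 0.35/2 = 0.175, the protocol's own planning value. There the omnibus test has 93% power and the all-four-pairs rule 54%.

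**The case against.** The strongest reply is that the plan does contain a success rule, and that its natural reading blocks the harm. Only one sentence says when the hypothesis is supported, and it names both Group 3 and Group 4. The pooled contrast appears only among comparisons meant to look at specific differences, next to 1 vs 3 and 2 vs 3, which do isolate the oil. This stands: the protocol never makes the pooled contrast decisive on its own. A reader might infer that the plan will declare success in 52–63% of trials without an oil benefit. The documents do not support that, because the figure holds only if the pooled contrast is taken as the test of the hypothesis.

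Three other strong readings also fail.

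- The 84% omnibus rate is not a rate of false oil claims. A real group difference exists in that scenario, and the success sentence is directional.
- The primary hypothesis is not about the oil alone. Sections 2.9 and 2.10 name both hypnosis alone and minimal intervention as comparators.
- The strict pairwise rule is not always badly underpowered. Its power is 54–83%, and 54% is the low end.

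It may also be said that the choice of multiplicity correction belongs in an analysis plan not shown here. That is accepted, and nothing here rests on it. It does not settle the main point, because an analysis plan that picked one rule would still conflict with other sentences of this protocol.

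**Conclusion.** The point holds in a conditional form. Sections 2.9, 2.10 and 2.13 give non-equivalent rules for one primary hypothesis. For a single truth (no oil effect, hypnosis d = 0.35, 105 per arm) the chance of meeting the rule runs from 0.4% to 92%, depending on the sentence followed.

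The pooled 1&2 vs 3&4 comparison contains half of any hypnosis effect and should not by itself support the hypothesis. The risk of false support depends on the reading, and the protocol leaves the reading open. Nor does the 80% power, computed for the omnibus test, carry over to the all-four-pairs reading: three of the four scenarios examined fall below it.

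The sizes rest on a borrowed hypnosis effect, R² = 0.20 and 105 analysed per arm. The algebraic point that the contrast equals d/2 when the oil adds nothing needs none of these figures.

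**What to change.** State one rule in sections 2.10 and 2.13, and align section 2.9 with it, before any unblinded analysis:

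1. The primary hypothesis is supported only if pooled Groups 1 and 2 exceed Group 3 *and* exceed Group 4 on baseline-adjusted T1 MDBF calmness, each at two-sided 0.05. Both are required, so α is not split. Use Groups 1–4 only, as in the planned primary analysis; Groups 5 and 6 stay out.
2. Then test each oil against Group 3 with Holm correction.
3. Keep the omnibus test and the pooled 1&2 vs 3&4 contrast as descriptive only.
4. State power for this rule at 105 analysed per arm: about 83% (d = 0.35) to 93% (d = 0.40) with no hypnosis effect, and 90–96% if hypnosis has an equal effect.

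Pooling the two oils is one valid choice among several. A rule that tests each oil separately would also do, provided it is fixed in advance and its own power is given.

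The cost is wording and a registry update, with no change to data collection. The rule has less power than the omnibus test (83% against 93% at d = 0.35 with no hypnosis effect), though not less than the stated 80% if 105 per arm are analysed.
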